#### 9.1.2 Methods

As patients are at home, we shall be using a new technology allowing measurement of the whole blood's genetic expression via a single drop of blood on a cotton swab taken by the patient himself from a finger. We have already demonstrated the validity of this approach in terms of RNA quality (RIN 6.9) and in accordance with the measures emerging from sampling by Tempus tube.

The following samples shall be taken:

- Day 0, Day 7, Day 14: 1 EDTA tube, 1 Tempus tube (total blood volume 3ml),
- Day 0, Day 1, Day 3, Day 5, Day 7, Day 9, Day 12, Day 14: 1 cotton swab

| Day                 | 0 | 1 | 3 | 5 | 7 | 9 | 12 | 14 |
|---------------------|---|---|---|---|---|---|----|----|
| Fresh blood (EDTA)  | X |   |   |   | X |   |    | X  |
| Serum (dry tube)*   | X |   |   |   | X |   |    | X  |
| Genes (Tempus tube) | X |   |   |   | X |   |    | X  |

---

Genes (cotton swab)    X X X X X X X X

---

\* 1 aliquot shall be reserved on the dry tube of the main study on Day 0, Day 7 and Day 14 for analysis of the functional profile.

### 9.1.3 Laboratory

**Cellular phenotypic profiles:** immunogenicity tests shall be carried out on the whole blood.

- Cells CD4+ and CD8+T are to be analysed for CD45RA expression and C-C chemokine receptor type 7 (CCR7), to identify the sub-populations of naive, memory and effector cells, and for the co-expression of activation markers, HLA-DR and CD38.
- The sub-populations of B cells are to be analysed with markers CD19, CD21, CD27, CD38, immunoglobulin (Ig) and IgM. Cells secreting antibodies are to be identified as CD19+ cells, expressing CD38 and CD27.
- The sub-populations of NK cells are to be analysed by means of CD16 and CD56 markers.
- HLA-DR, CD33, CD45RA, CD123, CD141 and CD1c are to be used in identifying DC sub-populations.

**Functional profiles, quantification of serum analytes:** Th1/Th2/activation/inflammation/apoptose markers are to be measured in serum by a Luminex assay, allowing the detection of more than 40 analytes with a commercial kit, according to the manufacturer's instructions. The Median Fluorescence Intensity for each sample is to be measured by means of the Bio-Plex 200 system (Bio-Rad, Marnes-la-Coquette, France). The Bio-Plex Manager version 6.0 software, which integrates a weighted adjustment of the logistical curves by five parameters, is to be used to calculate the concentrations of samples.

**Genetic expression profiles (whole blood sampled by Tempus tube and cotton swab):** Genetic expression profiles are to be analysed by RNA sequencing. RNA extraction is to occur according to the Illumina protocol before being sequenced on a HiSeq 2500 V4 system from Illumina. FastQ forms allow the identification of genes differentially expressed by use of normalised reading counts as input for Gene-Specific Analysis (GSA) carried out on the Partek® Flow® and R software.

### 9.1.4 Scale of the study

The number of people participating in this study is to depend on the take-up rate.

In total, 30 patients/arms with all measures (maybe 150 in total). This scale of sampling allows description of the phenotypic and functional profile of each arm upon inclusion and evolution over time with enough precision (72,73).

In the event of good take-up, the study of the genetic expression profile on cotton swabs could be proposed for all patients included in the main study. 20 to 40 events per treatment group are expected, which would make 100 to 200 events in total at the end of the trial, if all the participants in the main trial agree to participate in this sub-study; possibly 10 to 20 clinical progression predictors are possible with the conservative rule of 10 events per predictor (74).

### 9.1.5 Statistical analysis

For each treatment arm, cellular phenotypic and functional profiles will be described (absolute count and proportion), at inclusion and over time. The evolution with time will be compared to baseline values using parametric and non parametric tests, taking into account the multiplicity of tests (False Discovery rate).

Inter-measure agreement between the samples made on Tempus tubes and on cotton-sticks on the 30 patients per group will be studied thanks to intra-class correlation and Bland & Altman graphical method.

The evolution of gene abundance over time will be studied separately on the different type of samples. Supplemental sampling points made available by auto-sampling with cotton-sticks will be analyzed according to the first results obtained at D0, D7 and D14. Statistical analysis will be performed i) gene by gene with a functional enrichment analysis of differentially expressed genes (Ingenuity Pathway) and ii) by gene groups (75).

In the sample of patients (30 per group) with all measures available, an integrative analysis will be performed to study the association between gene abundance and other immunological and virological markers.

The association between biomarkers and clinical evolution will be adjusted on genic expression at inclusion and over time as well as on clinical and biological predictors.

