| NUMBER OF PARTICIPANTS                                              | 
 
- 169 participants in each of the 5 arms in people who were not on basic therapy with IEC or ARA2 before inclusion, i.e. 845 patients in total if the 5 arms are maintained until the end.
 
- 53 participants in each of the 4 arms (excluding telmisartan) in people who were on treatment with IEC or ARA2 before inclusion, i.e. 212 more patients if the 4 arms are maintained until the end.
 
 
The final number will depend on the number of arms that will continue after the intermediate analyzes and could not exceed 1057 participants
 |
| EXPECTED BENEFITS                                                   | Treatments to prevent complications of COVID-19 in the elderly. French hospitals are overwhelmed with new COVID-19 patients and it is expected that beds in the intensive care units will run out in the near future. Finding an effective treatment that can be administered at home to avoid hospitalization and transfer to intensive care is of critical importance.                                                                                                                                                                                                                                        |
| SIMULTANEOUS PARTICIPATION IN ANOTHER RESEARCH AND EXCLUSION PERIOD | 
The inclusion and simultaneous participation in any other interventional study is not authorized in order not to interfere with the results of this research.
 
No exclusion period is necessary following this research.
                                                                                                                                                                                                                                                                                                                                                                           |

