### 9.1 Immunological sub-study

The immunological sub-study has three explanatory objectives:

- evaluating the impact of study drugs on immunological parameters.
- identifying the immune biomarkers associated with clinical worsening.
- identifying the immune biomarkers associated with a change of the effect of those interventions evaluated.

In relation to the main study, it involves two things: (i) sampling of additional blood tubes on Day 0, Day 7 and Day 14 (additional 3ml); (ii) daily sampling of blood drops on a cotton swab (8 in total during the follow-up). This is only a gesture, yet whose enactment could prove difficult for certain people, or undesired by others in this particular context. It shall therefore be carried out by a sample of volunteers and subject to specific consent.

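### Section 9.1.5 names only within-arm tests against baseline for the immune profiles, although the sub-study's first objective is the effect of the drugs

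*Protocol*

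**What the plan says.** Protocol section 9.1 lists three objectives for the immunological sub-study. The first is "evaluating the impact of study drugs on immunological parameters".

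Section 9.1.5 opens with a by-arm description: "For each treatment arm, cellular phenotypic and functional profiles will be described (absolute count and proportion), at inclusion and over time". The test follows: "The evolution with time will be compared to baseline values using parametric and non parametric tests", with the addition "taking into account the multiplicity of tests (False Discovery rate". Gene expression is likewise to be studied as evolution over time. No part of 9.1.5 states a contrast between an experimental arm and the control arm.

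Section 9.1.4 sets the size: "In total, 30 patients/arms with all measures (maybe 150 in total". The reason given is descriptive: "This scale of sampling allows description of the phenotypic and functional profile of each arm upon inclusion and evolution over time with enough precision". No effect size, standard deviation, alpha or power is stated for the immune markers.

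Two places outside section 9 bear on the point. Section 4.3.2 lists changes in immunological markers from Day 0 to Day 7 and Day 14, in each group, among the trial's secondary criteria. Section 6.3.1 says that arms will be compared systematically, with and without adjustment.

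**The concern.** Whether a drug affects an immune parameter is a causal question, and in a randomised trial the comparison with control answers it. The stated test asks something else: whether the parameter moved between D0 and a later day within one arm.

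Participants enter early in an acute infection and are sampled at D0, D7 and D14. The protocol's own rationale (9.1.1) ties these markers to the severity and course of the disease. Some of them may therefore move in every arm, including the vitamin arm, without any drug effect. Section 9.1.1 also proposes reduced hyperinflammation as a route by which treatment could work, and recovery alone could produce the same fall.

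False Discovery Rate control does not address this. It limits the share of wrong rejections of the hypothesis being tested, which here is no change over time. If a marker moves naturally, rejecting that hypothesis is correct and says nothing about the drug.

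At stake is whether the sub-study, analysed as 9.1.5 states, can answer its first objective.

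**Working it through.** **1. The plan's own figures reproduce.** Size: 5 arms × 30 = 150. The number of arms comes from the Summary ("169 participants in each of the 5 arms"). Events: section 9.1.4 says "20 to 40 events per treatment group are expected, which would make 100 to 200 events in total at the end of the trial", and 5 × 20 = 100, 5 × 40 = 200. The per-group range fits the main-trial assumptions in 6.2.1 (25% in control, halved by an effective drug): 169 × 0.125 = 21 and 169 × 0.25 = 42. Predictors at 10 events each: 100/10 = 10 and 200/10 = 20. Nothing is wrong with these figures.

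**2. Inputs for the check.** n = 30 per arm is from 9.1.4. The 5% two-sided level, the paired t-test and the natural change m (in SDs of the change score) are assumptions, because the protocol gives no values for the immune markers. The true drug effect is set to zero.

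**3. Within-arm test of an inert drug.** The test statistic follows a non-central t distribution with 29 degrees of freedom and non-centrality m × √30. The critical value is 2.045.

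| Natural change m (SD) | Non-centrality | Probability of a significant result |
|---|---|---|
| 0 | 0 | 5.0% |
| 0.2 | 1.10 | 18.5% |
| 0.3 | 1.64 | 35.5% |
| 0.5 | 2.74 | 75.4% |
| 0.8 | 4.38 | 98.8% |

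These are rates for a single uncorrected test.

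**4. Comparison with control, same setting.** If both arms change by m, the expected difference in change is zero whatever m is. In 20,000 simulated pairs of arms (30 against 30), the between-arm t-test of change was significant in 4.8%, 5.2% and 4.9% of runs at m = 0, 0.5 and 1.

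**5. Reading the arms side by side is no substitute.** One might call a drug active when its own arm is significant and the control arm is not. For an inert drug at m = 0.5 the probability of that pattern is 0.754 × (1 − 0.754) = 18.5%; the simulation gave 18.4%.

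**6. What the randomised contrast can detect.** By the normal approximation, the difference in change detectable with 80% power is (1.960 + 0.842) × √(2/30) = 0.72 SD per marker, two-sided 5%, before False Discovery Rate control. Power is 21% at 0.3 SD, 49% at 0.5 SD and 87% at 0.8 SD.

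**The case against.** The strongest reply is that the protocol already provides the comparison. Section 4.3.2 makes changes in immunological markers a secondary criterion, section 6.3.6 analyses secondary endpoints by intention to treat on available data, and section 6.3.1 makes between-arm comparisons the general rule, with named tests and adjusted linear models. This stands in part: it would be wrong to say that the protocol as a whole never compares the arms on these markers. It does not remove the defect. Section 9.1.5 is the specific analysis for the sub-study, carries its own tests and multiplicity method, and does not refer to 6.3.1. The False Discovery Rate is attached to the baseline tests, and nothing says which analysis answers the first objective.

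A reader might infer that natural recovery will be reported as a drug effect. The documents do not support that. No passage says how a within-arm change will be interpreted, and 9.1.4 and 9.1.5 are partly framed as description.

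A reader might also take 75% or 99% as the expected share of markers falsely declared. That is not supported either. Those rates need a natural change of 0.5 or 0.8 SD in the marker concerned, and nothing shows that every cell subset and analyte moves that much. They also ignore the multiplicity correction.

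Finally, the exact model may be left to the statistical analysis plan, and the sub-study is still in preparation. That is fair for the model. The protocol has nevertheless stated a test, and that test does not fit the stated objective.

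**Conclusion.** The point holds in limited form. The only test that 9.1.5 names for the phenotypic and functional profiles is change from baseline, with no contrast between arms, and that test cannot isolate an effect of the drugs. The size of the problem depends on how far a marker moves by itself. For an inert drug with 30 per arm, the rate of significant within-arm results runs from 5% with no natural change to 98.8% at 0.8 SD. This assumes paired t-tests, a two-sided 5% level and no correction. A comparison with control stays near 5% throughout.

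The general rule in 6.3.1 and the criterion in 4.3.2 point the right way, so the repair is to bring 9.1.5 into line with them. The consequence is confined to a volunteer sub-study and does not touch the primary analysis, the interim rules or the main sample size. The change should be made before the sub-study starts.

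**What to change.** In section 9.1.5:

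- Name as the analysis of the first objective the difference between each experimental arm and the concurrent control arm at D7 and D14, adjusted for the D0 value.
- Apply the False Discovery Rate to those contrasts.
- Keep within-arm change as description.
- Refer to 4.3.2 and 6.3.1, so that the three sections give one instruction.

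The cost is wording only. The control arm is among the arms to be sampled, so no further samples or participants are needed, and section 9 says the sub-studies are still in preparation. The downside is modest power: about 0.72 SD is detectable with 80% power before correction. Results should therefore be reported as estimates with confidence intervals, and a non-significant contrast should not be read as absence of effect.

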## 9.2 Feasibility and take-up sub-study

### 9.2.1 Justification

The urgent implementation of the screening, home-treatment and follow-up model foreseen by the trial poses enormous challenges of logistical and human feasibility and gives rise to questions regarding the acceptability of activities undertaken, as much from the point of view of patients as general practitioners, other carers and mobilised research teams. The more often the constraints and opportunities are documented at each stage of the model being implemented, the more corrective solutions can be adopted and lessons learned for the transferability into other contexts. The more the intended model is well-accepted by the different stakeholders, the more it will be likely to be implemented as intended and thus be more effective. The idea of this sub-study is to use the principles of research on the implementation (document the main elements of acceptability and feasibility) to describe rapidly the roll-out of the clinical trial and inform its implementation (76).

### 9.2.2 Methods

Mixed methods are to be used to provide measures of logistical, human and technical resources; to document patients' and clinicians' experiences, interactions between patients and clinicians, interactions between patients and mobile teams, obstacles/facilitators to treatment and care, the perception of the quality of care; the general context of implementing this model shall also be documented to describe its influence on the effectiveness of implementation and transferability of the model in different contexts. More precisely:

- A short questionnaire on acceptability shall be offered to all participants on Day 3, Day 5 and Day 9;
- A brief individual targeted interview shall be held with 5 to 8 participants on Day 3
- Group discussions are to be organised with the implementation teams in the field, in order to document the daily challenges and opportunities and react quickly to logistical changes.

The quantitative feasibility and acceptability data is especially to be based on:

- Data drawn from the acceptability questionnaire at the participant level
- Process indicators:
  - number of face-to-face visits carried out in relation to the number foreseen (by indicating constraints at the patient or care team level)
  - duration of face-to-face visits
  - duration of patient follow-up
  - changes in the staff involved (number, profile and training)
  - equipment used
  - costs

Qualitative data on feasibility and acceptability shall be analysed according to a pragmatic approach to the method of “thematic analysis”, guided by the predefined themes on individual and group interviews. Results are to be summarised according to the main themes and interpreted, in order to formulate recommendations on the implementation of phase III of the trial.

Quantitative data from the questionnaire and qualitative from the interviews shall be integrated into the management, backup and confidentiality system for all trial data.

## 9.3 Data management

All activities linked with the management and security of data are to be described in the trial's data management plan.

### 9.3.1 Data management software

The electronic tool for online randomisation has been developed by the Inserm team U1219 on the ASP.NET/SQLServer. This tool and its database are hosted on servers at the Inserm Centre, U1219/ISPED, which are administered by the Centre's IT Department.

The software in use for data management is REDCap. It is linked to a dedicated MySQL database.

IT Systems Management (DSI) at CHU de Bordeaux assures hosting and maintenance of the database in accordance with its procedures. The servers (Internet and database) are hosted within the DSI of the CHU de Bordeaux (Talence, Gironde, France)

### 9.3.2 Source data

Apart from the biological examination results, patient data shall be entered directly into the e-CRF and shall as a result have no source data.

### 9.3.3 Data security

Access to the private site for randomisation is secured, controlled and traced; authentication is reserved for team members and the administration of the user accounts assured by the project's IT team. Access to the complete randomisation list is exclusively reserved for the project's statisticians.

All information on participants shall be strictly confidential. Information, such as the participant's name or any other data able to lead to identification of the participant, shall not be recorded in the trial's database.

All paper documents and digital forms necessary for data management are reserved for authorised trial staff.

The trials' database shall only be accessible by means of personal user name and password. Management of access rights to the software is the responsibility of the REDCap administrator at the CHU de Bordeaux. A list of authorised users of the database shall be updated during the study.

### 9.3.4 Entry and control of data

Entry of data into the eCRF shall be the responsibility of the Centre's researcher. All persons carrying out entries to the eCRF or carrying out requests for online randomisation shall be trained beforehand and delegated by the coordinating investigator to do so. A guide to using the various tools shall be drawn up. Data shall be recorded by means of tablets (mobile teams) and computers (outpatient COVID-19 testing unit). Controls shall be programmed in, so as to check the coherence and completeness of data entered into the eCRF. Prescribed treatments and clinical events are encoded in order to be able to carry out the control and analysis of data.

### 9.3.5 Control of AE/SAE databases

The crossover of databases shall be supervised by the Safety and Monitoring Unit (SMU) of the CHU de Bordeaux, according to the procedure in effect within the EUCLID team. Comparisons shall be carried out regularly, according to a schedule defined by the DSMB. The Data Manager shall be responsible for sending the table of adverse events to the Safety and Vigilance Monitoring Unit.

### 9.3.6 Setting the database

The database shall be set for the final analysis. Setting of data is to be carried out in compliance with the procedure in effect.

### 9.3.7 Archiving of the database

Archiving of the database shall be the responsibility of the study's sponsor. Data from the study shall remain stored on the DSI server at the CHU de Bordeaux, in compliance with the regulations in effect for the study. A physical copy shall be retained by the sponsor in compliance with regulations in effect.

### 9.3.8 Quality management

The data management plan for the trial and the procedure manual are to describe in detail:

- the system used to digitise the data
- those methods permitting guarantees of restricted access to the database, backup of data and confidentiality
- procedures relating to the titling of data, tracing of data, incident management and best practices in matters of IT security.

### 9.3.9 Confidentiality and security of participants' data

All information on participants shall be strictly confidential. Information, such as the participant's name or any other data able to lead to identification of the participant, shall not be recorded in the trial's database.

All paper documents and digital forms necessary for data management are reserved for authorised trial staff, as much at the international level as the local. The trials' database shall only be accessible by means of personal user name and password. A list of authorised users of the database shall be held by the CTU and updated during the study.

## 9.4 Monitoring

### 9.4.1 Clinical Trial Unit (CTU)

The monitoring team shall comprise of an international CTU and a national CTU by participating country.

The International CTU is to assure international monitoring, including remote data monitoring, on-site visits and the centralised multi-country monitoring, according to a monitoring plan established earlier. It shall be constituted of team members from MEREVA and EUCLID.

The National CTU is to assure monitoring of the country, including remote data monitoring, on-site visits and the centralised country monitoring, according to a monitoring plan established earlier.

The monitoring team is to supervise the roll-out of the trial to verify that:

- The rights, safety and well-being of the trial's participants are protected
- The recorded and analysed data is precise, complete and coherent
- The trial is held in compliance with the applicable protocol, Normalised Standard Operating Procedures (NSOP), Good Clinical Practices (GCP) and regulatory requirements

